## Abstract

**Background:**

Previous studies have shown that electroacupuncture (EA) reduces the severity of acute pancreatitis. However, the effect of EA for pain relief in patients with acute pancreatitis has not been evaluated yet. The purpose of this study was to prove the efficacy of EA for pain relief in patients with acute pancreatitis compared with conventional treatment.

**Methods:**

This study is a randomized, controlled, three-arm, parallel-group, multi-center trial. Patients diagnosed with acute pancreatitis are enrolled and randomly assigned to EA 1, EA 2, or a control group in a 1:1:1 ratio. All the enrolled patients basically receive the conventional standard-of-care therapy for acute pancreatitis. Local EA is given in group EA 1, while local with additional distal EA is given in group EA 2. Local EA includes two acupoints, *Zhong Wan* (CV12) and *Shang Wan* (CV13), located in the abdomen, while distal EA includes 12 peripheral acupoints, *Zhong Wan* (CV12), *Shang Wan* (CV13), *He Gu* (LI4), *Nei Guan* (PC6), *San Yin Jiao* (SP6), *Xuan Zhong* (GB39), *Zu San Li* (ST36), and *Shang Ju Xu* (ST37). The patients randomized to the EA 1 and EA 2 groups undergo one session of EA daily from day 1 until day 4, or until pain resolves. The primary endpoint is the Visual Analog Scale (VAS) change for pain on day 5. Secondary endpoints include daily VAS, requirement of analgesics, changes of inflammatory markers, time to pain disappearance, and hospital days.

**Discussion:**

The results of this trial are expected to prove the efficacy of EA for pain relief in patients with acute pancreatitis. Based upon the results, EA would be applied to a variety of clinical practices for reducing pain.

**Trial registration:**

This trial is registered at ClinicalTrials.gov, ID: NCT03173222. Registered on 1 August 2017.

**Electronic supplementary material:**

The online version of this article (10.1186/s13063-018-2644-1) contains supplementary material, which is available to authorized users.

## Background

The prevalence of acute pancreatitis (AP) is increasing due to cholelithiasis and increased alcohol consumption [1]. While the overall mortality in all hospitalized patients with AP is approximately 10%, the mortality in the subset with severe AP may be as high as 30% [2]. AP causes significant abdominal pain, which can adversely affect patients’ quality of life. Most patients have associated nausea and vomiting [3]. Pain control for such patients is the mainstay of AP management.

Opioids are safe and effective for pain control in patients with AP. Compared with other analgesic options, opioids may decrease the need for supplementary analgesia [4]. However, frequent administration of opioid analgesics may result in opioid dependency [5, 6]. In the United States, there has been a tripling in the rate of opioid-related overdose deaths from 2000 to 2014, with over 28,000 deaths in 2014 [7]. This epidemic creates a dilemma for physicians who seek to provide adequate pain relief while minimizing risks of abuse and dependency [8]. Unfortunately, any innovative treatment for better analgesia than opioids has not been developed in medical science so far. Therefore, the development of a novel treatment for pain relief without triggering dependency is urgent.

Acupuncture originated in China approximately 2,000 years ago and is one of the oldest medical procedures in the world. Acupuncture continued to be developed and codified in texts over the subsequent centuries and gradually became one of the standard therapies used in China. Later, acupuncture was introduced to other regions including Asia, Europe, and the United States [9]. The most thoroughly studied application of acupuncture is for pain relief [10]. The proposed mechanism of action was that acupuncture stimulation is associated with neurotransmitter effects such as endorphin release [11]. In this sense, acupuncture within oriental medicine could be an appropriate alternative for opioid analgesics, since it has been known as an effective treatment for pain relief without dependency. Electroacupuncture (EA) is a form of acupuncture where a small electric current is passed between pairs of acupuncture needles. Previous studies have suggested that EA blocks pain by activating a variety of bioactive chemicals through peripheral, spinal, and supraspinal mechanisms [12]. A recent clinical trial showed that EA reduced the duration of postoperative ileus, time to ambulation, and postoperative analgesic requirement, compared with no or sham acupuncture, after laparoscopic surgery for colorectal cancer [13]. Another study indicated that EA may reduce the severity of AP by inducing anti-inflammatory effects [14]. However, to the best of our knowledge, the effect of EA for pain relief in patients with AP has not been evaluated yet. Therefore, we planned to prove the efficacy of EA for pain relief in patients with AP compared with conventional treatment.

## Methods

### Study design and ethical considerations

This study is a randomized, controlled, three-arm, parallel-group, prospective, multi-center trial conducted for the purpose of comparing and analyzing the efficacy of pain relief between conventional treatment and EA + conventional treatment in patients with abdominal pain who are diagnosed with AP. It is designed as a three-arm, parallel-group, superiority trial. All participating hospitals are teaching hospitals, which have both College of Medicine and College of Korean Medicine recognition. This study was approved by the Institutional Ethics Review Board (IRB) of Dongguk University Ilsan Hospital (IRB No. 2017-50; Dongguk University Ilsan Oriental Hospital, 2017-06). Based on the Helsinki Declaration, the health and human rights of subjects will be prioritized and voluntary written consent will be obtained from all subjects before entering clinical studies. We will obtain all informed consents after 30 min of explanation. Records identifying the subject’s identity will be kept confidential.

### Inclusion criteria

Inpatients who meet the following requirements are eligible for enrollment: (1) diagnosed with AP; the definition of AP is based on the fulfillment of two out of three of the following criteria: clinical (upper abdominal pain), laboratory (serum amylase or lipase > 3× upper limit of normal) and/or imaging (computed tomography, magnetic resonance imaging, ultrasonography) criteria [2]; (2) aged ≥ 20 years; (3) understand the nature and the risks involved in the study and are able to communicate with the investigators; and (4) signed the written informed consent by listening to the explanation of the purpose, methods, and effects of this study.

### Exclusion criteria

Participants with any of the following conditions are excluded: (1) severe AP with multi-organ failure; (2) history or intolerance to EA; (3) pregnant or breast-feeding women; (4) informed consent could not be obtained; and (5) considered to be difficult to perform this clinical trial when judged by the principal investigator.

### Randomization

Patients will be randomized in a 1:1:1 fashion to receive EA1, EA2, and the control group. Block randomization is performed using Random Allocation Software version 1.0.0. A person who is not involved this study creates random numbers before the first subject enrolls after IRB approval. Then, the random numbers are kept in sealed envelopes in the order of their creation. An independent hospital staff member will prepare the sealed envelopes to ensure concealment of the allocation sequence. The numbers are handed over to assistants (independent researchers). After randomization, the treatment method is not blinded.

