### Statistical analysis

The statistical analysis will be based on the intention-to-treat (ITT) population. Missing data imputation will be used in order to evaluate the robustness of the primary endpoint analyses. The primary imputation method will be LOCF (last observation carried forward). The statistical analysis will be conducted for both three (EA 1: EA 2: control) and two (EA: control) groups. The null hypothesis is that there is no difference in the changes of variables between the two or three groups before and after treatment. The three groups will be compared by one-way analysis of variance (ANOVA) or the Kruskal-Wallis test for continuous variables, and chi-squared or Fisher’s exact test for categorical variables. Analysis of covariance will be performed with covariates that may affect VAS level. Post hoc analysis will be done if there is a significant difference between the three groups using the Bonferroni correction. The two (EA: control) groups will be compared by means of Student’s *t* test or Wilcoxon’s rank sum test for continuous variables, and chi-squared or Fisher’s exact test for categorical variables. A two-sided *P* value of less than 0.05 will be considered to indicate statistical significance.

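### The named tests for the day-5 VAS change adjust for neither pretreatment VAS nor centre, and the planned ANCOVA has no fixed covariates or status: a loss of precision, not of validity

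*Protocol article*

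**What the plan says.** Under Study design and ethical considerations the trial is a "three-arm, parallel-group, prospective, multi-center trial". More than one hospital takes part ("All participating hospitals are teaching hospitals"), but the number is not given. Under Randomization, "Patients will be randomized in a 1:1:1 fashion to receive EA1, EA2, and the control group" and "Block randomization is performed using Random Allocation Software version 1.0.0". The article does not say whether the blocks were made per centre. The same section adds: "After randomization, the treatment method is not blinded".

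Under Outcomes the primary endpoint is the change in VAS (0–100) from pretreatment to day 5, so each patient's pretreatment VAS is collected.

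Under Statistical analysis, "The three groups will be compared by one-way analysis of variance (ANOVA"), with Kruskal-Wallis as the alternative. EA against control is compared by Student's t test or Wilcoxon's rank sum test. All four tests use treatment group only. The section then adds: "Analysis of covariance will be performed with covariates that may affect VAS level". It does not name the covariates, and it does not say how this analysis ranks against the ANOVA and t test.

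**The concern.** Two known sources of variation are outside the named comparisons.

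- **Pretreatment VAS.** Subtracting it fixes its regression coefficient at 1. When the correlation between pretreatment and day-5 VAS is moderate, that over-corrects and adds noise. ANCOVA estimates the coefficient instead.
- **Centre.** EA is delivered by an operator and analgesics are stepped up as required, so some difference between hospitals is plausible. Without a centre term that variation stays in the error. Under a single allocation list, a chance imbalance in centre also stays in the realised estimate.

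The ANCOVA could deal with both. As written, however, neither its covariates nor its place in the hierarchy is settled. In an open trial with a patient-reported endpoint, that is better fixed before data are seen.

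**Working it through.** **Inputs from the article (Planned number of subjects and period; Statistical analysis):** SD 19 (test) and 25 (control), difference 20, power 90%, two-sided 5%, 25 evaluable per arm, 20% dropout, 33 randomised per arm, 99 in total.

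**Inputs assumed:** correlation ρ between pretreatment and day-5 VAS of 0.2 to 0.7; intra-centre correlation (ICC) of 0.02 to 0.15; 2 to 4 centres; blocks of 6.

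**1. The plan's own figure.** n = (19² + 25²)(1.960 + 1.282)² / 20² = 986 × 10.51 / 400 = 25.9, so 26 per arm against the stated 25. Dropout: 26 / 0.8 = 32.5, so 33 per arm and 99 in total, as stated. The root-mean-square SD is √(986/2) = 22.2. The calculation has no baseline or centre component, so this point does not make it wrong.

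**2. Pretreatment VAS.** Let the pretreatment and day-5 SDs both equal σ.
- Change-score variance: 2σ²(1 − ρ).
- ANCOVA residual variance: σ²(1 − ρ²).
- Ratio: 2(1 − ρ)/(1 − ρ²) = 2/(1 + ρ).

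| ρ | Change-score variance ÷ ANCOVA variance |
|---|---|
| 0.2 | 2/1.2 = 1.67 |
| 0.5 | 2/1.5 = 1.33 |
| 0.7 | 2/1.7 = 1.18 |

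In patients, 25 per arm under ANCOVA carries the information of about 25 × 1.18 = 29 to 25 × 1.67 = 42 per arm under the change-score test. With unequal SDs σ₀ (pretreatment) and σ₁ (day 5), the change-score variance exceeds the ANCOVA variance by (σ₀ − ρσ₁)². That is never negative, so apart from one degree of freedom ANCOVA does not lose. I leave the gain as a variance ratio because the article does not say whether 19 and 25 are SDs of the change or of a single VAS.

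**3. Centre.** One EA arm against control was simulated with total SD 22.2 and a difference of 20. The test was run with and without a centre term at the same ICC.

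| Setting (26 per arm, 2 to 4 centres) | Change in power from adding centre |
|---|---|
| One unstratified list, ICC 0.02–0.05 | about −2 to +0.3 points |
| One unstratified list, ICC 0.10–0.15 | +0.2 to +2.3 points |
| Blocks made per centre | about 0 to +2 points |

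The loss at low ICC arises with four centres and one list. The term then uses degrees of freedom and some balance between treatment and centre, with little variance to remove.

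**4. Validity without centre.** At 25 per arm, mean bias was about 0 in every setting. At 26 per arm, type I error was about 5% with one list, and 3.7 to 4.4% when blocks were made per centre and centre was ignored (ICC 0.15).

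**5. Size of a chance imbalance.** Suppose two centres differ by 10 VAS points and their shares are 60/40 in one arm and 40/60 in the other. The unadjusted difference then moves by 10 × (0.6 − 0.4) = 2 points, against a target of 20.

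**The case against.** The strongest reply is that nothing here is an error. An unadjusted comparison in a randomised trial is valid, and steps 1 and 4 bear that out. The ANCOVA wording is broad enough to include both pretreatment VAS and centre, and a condensed article may leave the covariate list to the analysis plan. Conduct also looks fairly uniform across hospitals: a common analgesic ladder, fixed acupoints, frequencies and session length, and one stimulator. Because the endpoint is a change, stable centre differences in how VAS is scored partly cancel.

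Most of this stands. The unnamed covariates and the unstated stratification are not defects in themselves, and a large ICC cannot be presumed. What remains is that the article does state its main comparisons, and states them on treatment group alone. A more precise analysis is available from data already collected.

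A reader might go further and infer that centre differences bias the result, that the sample size is wrong, or that a centre term is better whatever the list. The documents do not support these readings. Imbalance under randomisation is random, 33 per arm and 99 in total follow from the article's inputs, and step 3 shows settings in which the centre term costs power.

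**Conclusion.** The point holds as one of efficiency, and is minor. The larger and more dependable gain is from pretreatment VAS: the change-score comparison has about 1.2 to 1.7 times the ANCOVA variance for ρ from 0.7 to 0.2, assuming equal variances at the two times. The gain from centre is small and conditional: about 0 to 2 power points at ICC 0.10 to 0.15, and no gain or a loss of up to about 2 points at ICC 0.02 to 0.05 with several centres on a single unstratified list. The number of centres, the ICC and ρ are all assumptions, since none is in the article. Randomisation and the planned 99 patients are unaffected.

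**What to change.** State that the primary day-5 VAS comparison is an ANCOVA with treatment and pretreatment VAS, for the three-group analysis and for EA against control, and that the unadjusted ANOVA and t test are supportive. The endpoint can remain the change: with pretreatment VAS in the model, analysing the change or the day-5 value gives the same treatment difference.

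Add centre as a fixed factor, pooling very small centres, if the blocks were made per centre or if there are only two or three centres. With more centres on a single list, it may be left out of the primary model. Fix this choice before analysis.

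The cost is a few sentences of analysis wording, one degree of freedom for pretreatment VAS, and one for each centre beyond the first if centre is included. Pretreatment VAS is already collected, and nothing in the randomisation or sample size changes.

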### Standard-of-care therapy

All the enrolled patients basically receive the conventional standard-of-care (SOC) therapy for AP. For the conventional therapy, first, non-steroidal anti-inflammatory drugs are administered; afterwards, if inadequately controlled, low-potency narcotic analgesics, such as codeine, and then high-potency narcotic analgesics, such as morphine, will be given sequentially as required [15].

### Interventions and electroacupuncture procedures

Local EA is given in group EA 1, while local with distal EA is given in group EA 2, additionally. The EA 1 group receives the same SOC therapy in combination with EA therapy at a total of two acupoints including *Zhong Wan* (CV12) and *Shang Wan* (CV13). The EA 2 group also receives the same SOC therapy in combination with EA therapy at a total of 14 acupoints including *Zhong Wan* (CV12), *Shang Wan* (CV13), *He Gu* (LI4), *Nei Guan* (PC6), *San Yin Jiao* (SP6), *Xuan Zhong* (GB39), *Zu San Li* (ST36), and *Shang Ju Xu* (ST37) (Fig. 1) [14, 16, 17]. Electric stimulation is applied with mixed frequencies (30 and 3 Hz). Each EA session lasts 15 min (STN-330 electronic stimulator, Stra Tek Co., Ltd., Gyeonggi-do, Korea). Both EA groups receive auricular acupuncture therapy at a total of five auricular acupoints, including Sympathetic, *Shen Men*, Abdomen, Pancreas gall, and Spleen, alternately at the right or left side, whenever EA is given. Both EA groups undergo one session of EA daily from day 1 until day 4, or until pain resolves.

**Fig. 1 Fig1:**
[figure not shown]
Locations of acupoints in electroacupuncture groups

### Outcomes

The primary endpoint is the change in Visual Analog Scale (VAS, 0–100) for pain on day 5 compared to pretreatment. Secondary endpoints include daily VAS (days 1–4), requirement of analgesics, changes of inflammatory marker (C-reactive protein), time to pain disappearance and hospital days. Daily VAS is the average of VAS measured three times a day. The requirement of analgesics includes both the amount and frequency of analgesics administered daily.

### Planned number of subjects and period

A total of 99 patients will be enrolled for 2 years. Sample size calculation was performed for achieving a 90% power at the 5% level of significance.. The sample size was calculated as in Fig. 2. The population standard deviation (*σ*) was determined as the largest value according to a previous study [18]. Therefore, the standard deviations are 19 for the test group and 25 for the control group. The expected minimum clinical difference of 20 has been defined; this is the difference between the test group and the control group. This is achieved by enrolling 25 evaluable patients in each treatment group. To allow for a possible 20% dropout rate, 33 patients will be randomised to each group. The enrolled patients will be followed up for 1 month to monitor any delayed adverse events (see Fig. 3 for the schedule of enrollment, interventions, and assessments..

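### The stated 90% power describes one unadjusted two-group comparison; under the planned Bonferroni step each EA arm has about 75–83% against control at the stated 25 evaluable patients per arm

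*Protocol article*

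**What the plan says.** The sample size section of the protocol article (Planned number of subjects and period) states: "Sample size calculation was performed for achieving a 90% power at the 5% level of significance". Its inputs are that "the standard deviations are 19 for the test group and 25 for the control group" and that "The expected minimum clinical difference of 20 has been defined", and it explains that "this is the difference between the test group and the control group". It continues: "This is achieved by enrolling 25 evaluable patients in each treatment group". On attrition: "To allow for a possible 20% dropout rate, 33 patients will be randomised to each group". Neither the three arms nor any multiplicity adjustment enters the stated calculation.

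The Statistical analysis section plans a three-group comparison (ANOVA or Kruskal-Wallis) and also a two-group comparison of both EA arms together against control, and does not say which is primary. The individual arms come in here: "Post hoc analysis will be done if there is a significant difference between the three groups using the Bonferroni correction". The general rule is "A two-sided *P* value of less than 0.05 will be considered to indicate statistical significance".

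**The concern.** The sample size appears to have been worked out for a trial with two groups and one test at 5%. The individual EA arms are then to be tested at a stricter level than the one that was sized. A reader who takes the 90% to cover a claim that EA 1, or EA 2, beats control would be misled. That question matters to this trial: the Discussion gives the comparison of local with distal EA as the reason for having two EA arms. The evaluable number also seems to have been rounded down, and it does not lead to the 33 randomised per arm.

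**Working it through.** **Inputs from the sample size section:** difference 20; SDs 19 (test) and 25 (control); power 90%; level 5%; 25 evaluable and 33 randomised per arm; dropout 20%. Two-sidedness comes from the Statistical analysis section.

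**1. Reproducing the plan's figure.** For one test group against control:

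n = (z for 1 − α/2 + z for power)² × (19² + 25²) / 20²

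- α = 0.05 two-sided: (1.960 + 1.2816)² × 986/400 = 25.9, so 26 per group.
- α = 0.05 one-sided: 21.1, so 22. This does not reproduce 25.

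The 90% therefore belongs to a single unadjusted two-sided comparison.

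**2. 25 or 26.**
- At n = 25 the standard error is √(986/25) = 6.28, and 20/6.28 = 3.185. Power is Φ(3.185 − 1.960) = 89.0%, or about 87.6% by the t distribution with separate variances.
- At n = 26: 90.1% (normal) or 88.9% (t).
- 26/0.8 = 32.5 gives the stated 33; 25/0.8 = 31.25 would give 32. The number randomised thus comes from 26.

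**3. Level of the arm-level tests.** The number of Bonferroni comparisons is not stated. Three (all pairs) means 0.05/3 = 0.0167; two (each EA arm against control) means 0.025. By the normal formula at n = 25:
- 0.0167: Φ(3.185 − 2.394) = 78.5%
- 0.025: Φ(3.185 − 2.241) = 82.7%

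**4. The rule as planned, by simulation.** At least 200,000 three-arm trials per setting; SDs 19/19/25; true difference 20 in both EA arms; overall F test at 5%; then the pairwise test. Power for one EA arm against control:

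| Evaluable per arm | Three comparisons, separate variances | Three comparisons, three-arm error variance | Two comparisons, separate / three-arm variance |
|---|---|---|---|
| 25 | 75% | 80% | 80% / 83% |
| 26 | 77% | 82% | 82% / 85% |
| 33 | 88% | 91% | 91% / 93% |

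The loss comes from the Bonferroni level. The F gate costs almost nothing: with separate variances and 25 per arm, power is 75.7% both with and without it when each pair is tested on 48 degrees of freedom (75.3% with Welch degrees of freedom). Power to show both EA arms superior, with three comparisons and separate variances, is about 65% at 25 and 67% at 26.

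**5. The two top-level tests at 25 per arm.**
- Three-group ANOVA: 91% if both arms work.
- Pooled EA (50) against control (25), Student's t: 95% if both arms work. If only one works the average effect is 20/2 = 10, and power is about 43%.

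**6. What 90% at the Bonferroni level would take.** (2.394 + 1.2816)² × 986/400 = 33.3, so 34 evaluable per arm (35 by t), which is 43–44 randomised per arm after 20% dropout.

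**7. The alternative of closed testing.** With three arms, an overall test at 5% followed by pairwise tests at 5% forms a closed procedure.
- Power per arm with separate-variance tests: 86% at 25 and 87% at 26.
- Error rate for an ineffective arm when the other works: 5.0% with separate variances, but 6.2% with the three-arm error variance, which averages in the smaller SDs.
- With no effect in either arm, the chance that the F test or the parallel pooled test is significant is 7.5% with equal SDs and 8.8% with SDs 19/19/25.

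**The case against.** The strongest reply is that nothing promises 90% for each EA arm. The sample size section speaks of one test group against control, the study design section describes the purpose as EA plus conventional treatment against conventional treatment, and the pairwise tests are labelled post hoc. Both top-level tests meet 90% at the planning values if both arms work. This stands. A reader might infer that the whole trial is underpowered for its primary analysis; the documents do not support that. What remains is that the text does not say which test the 90% covers, and it is wrong if read as covering the arms.

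A single figure of about 76% would also claim too much. The number of comparisons and the error variance are not fixed. The intention-to-treat analysis with last observation carried forward may include all 33 per arm, which gives 88–91% with three comparisons. That is an upper bound, because imputed values may carry less information, and the protocol bases its own claim on 25 evaluable. The planned covariance analysis could also change power; the documents give no figure for it.

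Finally, Bonferroni after ANOVA is conservative but legitimate. A reader might infer that it buys nothing and must go. That holds only for separate-variance pairwise tests, and removing it leaves the parallel pooled test uncontrolled.

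The difference between 25 and 26 is small and leaves enrolment unchanged. It is still an inconsistency within one paragraph.

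**Conclusion.** The point holds for the arm-level comparisons. The stated 90% applies to one unadjusted two-sided two-group test and needs 26 evaluable per group, not 25. For EA 1 or EA 2 against control under the planned Bonferroni step, power at 25 evaluable is 7 to 15 points below the stated 90%, depending on the number of comparisons and the error variance. These figures assume normal data, the protocol's difference and SDs, and an SD of 19 in both EA arms. The pooled test does not rescue the arm-level question, since its power more than halves if only one arm works. This is a misstatement of power: it shows neither that the enrolment is wrong nor that the Bonferroni step is an error.

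**What to change.** In the sample size section:

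1. Correct 25 to 26 evaluable per arm; 33 randomised then follows.
2. State which comparison the 90% applies to.
3. State the number of Bonferroni comparisons and the resulting arm-level power: about 77–82% at 26 evaluable with three comparisons.

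Optionally, and before any analysis, replace the Bonferroni step by closed testing for three arms: the overall test at two-sided 5%, then separate-variance pairwise tests at two-sided 5%, with about 86–87% power per arm at 25–26 evaluable. This is sound only if the pooled EA-versus-control test is made secondary or brought under the same error control.

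The cost is wording and a stated power less favourable than 90% for the individual arms. No extra patients are needed, unless the trial wants 90% for each arm under Bonferroni with three comparisons, which would take 43–44 randomised per arm.
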